## Version History

| Version | Date              | Primary Author/Reviewer | Description                                                                                                                                                                                        |
|---------|-------------------|-------------------------|----------------------------------------------------------------------------------------------------------------------------------------------------------------------------------------------------|
| 0.1     | January 22, 2021  | [name]         | 1 st Draft Submitted to Moderna for review                                                                                                                                              |
| 0.2     | February 9, 2021  | [name]         | 2 nd Draft Submitted to Moderna for review                                                                                                                                              |
| 1.0     | February 17, 2021 | [name]         | Final Draft Submitted to Moderna for review                                                                                                                                                        |
| 1.1     | May 21, 2021      | [name]         | Draft Submitted to Moderna for review – Update: Addition of adolescents (12-17 years); addition of timing of select secondary analyses; clarifications in response to questions from EMA and CBER. |
| 2.0     | June 4, 2021      | [name]         | Final Draft Submitted to Moderna for review                                                                                                                                                        |
| 2.1     | August 4, 2021    | [name]         | Draft Submitted to Moderna for review – Update: Addition of vaccine effectiveness against SARS-CoV-2 variants.                                                                                     |
| 3.0     | September 7, 2021 | [name]         | Final Draft Submitted to Moderna for review                                                                                                                                                        |

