#### Inclusion criteria

- Aged  $\geq 12$  years at index date
- KPSC member for  $\geq 12$  months prior to index date through 14 days after the index date (allowing a 31-day gap)  
Membership is necessary to follow-up individuals for COVID-19 outcomes in the EHR. In addition, prior membership allows comorbidities and other covariates to be identified and considered in analyses as potential confounders.

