### 7.3 Other Variable Definitions

Other variables (Table 3) will be identified from EHR and considered in analyses when feasible and appropriate as covariates or stratification variables.

Table 3. List of possible covariates

|                                                                                                  | Categories                                                                                |
|--------------------------------------------------------------------------------------------------|-------------------------------------------------------------------------------------------|
| Variables to be assessed at index date (Day 0)                                            |                                                                                           |
| Age at index date, years                                                                         | 12-17, 18-44, 45-64, 65-74, 75+                                                           |
| Sex                                                                                              | Female, Male                                                                              |
| Race/Ethnicity                                                                                   | Non-Hispanic White, Non-Hispanic Black, Non-Hispanic Asian, Hispanic, Other/Unknown       |
| Month of index date                                                                              | By calendar month                                                                         |
| Socioeconomic status                                                                      |                                                                                           |
| Medicaid                                                                                         | Yes, No                                                                                   |
| Neighborhood median household income                                                             | To be determined based on variable distribution                                           |
| Medical center area                                                                              | MC1, MC2, MC3, ...                                                                        |

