| Pregnancy status                                                                                 | Yes (1 st trimester, 2 nd trimester, 3 rd trimester), No |
| Variables to be assessed in the two years prior to index date (-730 to -1 day, inclusive) |                                                                                           |
| Any smoking behavior                                                                             | Yes, No, Unknown                                                                          |
| Most recent Body Mass Index (BMI) measurement                                                    | <18.5, 18.5 - <25, 25 - <30, ≥30 - <35, 35 - <40, 40 - <45, ≥45, Unknown                  |
| Variables to be assessed in the year prior to index date (-365 to -1 day, inclusive)      |                                                                                           |
| Charlson comorbidity score [14]*                                                                 | 0, 1, 2+                                                                                  |
| Autoimmune conditions                                                                     |                                                                                           |
| Rheumatoid arthritis                                                                             | Yes, No                                                                                   |
| Inflammatory bowel disease                                                                       | Yes, No                                                                                   |
| Psoriasis                                                                                        | Yes, No                                                                                   |
| Psoriatic arthritis                                                                              | Yes, No                                                                                   |
| Multiple sclerosis                                                                               | Yes, No                                                                                   |

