1. The distribution of covariates will be reviewed. Some categories of a categorical variable with small sample sizes may be redefined or combined into one category.
2. The association of baseline covariates with exposure will be assessed. We will use standardized difference to assess the balance of covariates between exposed and unexposed cohorts. Unlike p-values, for which magnitude is highly related to sample size, standardized difference is a unified approach to quantifying the magnitude of difference between groups regardless of sample size, where an absolute value less than 0.1 is considered a negligible difference. Potential confounders will be determined by absolute standardized difference (ASD) >0.1.
3. All potential confounders from Step 2 will be included in the analyses. Steps 1 and 2 will be repeated for the 2-dose cohort and the 1-dose cohort. Matching variables (age, sex, race/ethnicity and index date), which are considered important risk factors, will be kept in the

adjusted model for possible imbalance on matching variables due to loss to follow-up or subgroup analysis (e.g., by baseline comorbidities).

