## 8.4 Secondary Analyses

Secondary analyses will be conducted for the 4th interim and the final analysis. Select secondary analyses will also be conducted for the 1st interim analysis (VE by age, sex, race/ethnicity, history of COVID-19, and asymptomatic COVID-19 [based on individuals with a positive result from a surveillance/asymptomatic test]) and for the 2nd interim analysis (VE in pregnant women).

For each secondary analysis, we will examine the distribution of index dates in vaccinated individuals; we will assign index dates by stratified variables so that the frequency distribution of their index dates matches that of vaccinated individuals.

**Secondary Objective 1:** For Secondary Objective 1, analyses will be stratified by sex and age category (12-17 years, 18-44 years, 45-64 years, 65-74 years, and 75+ years) at index date. For each stratum, we will calculate COVID-19 diagnosis incidence, unadjusted and adjusted HRs and VEs, as described for the primary analysis above.

**Secondary Objective 2:** For Secondary Objective 2, analyses will be stratified by race/ethnicity (Non-Hispanic White, Non-Hispanic Black, Hispanic, and Non-Hispanic Asian). For each stratum, we will calculate COVID-19 diagnosis incidence, unadjusted and adjusted HRs and VEs, as described for the primary analysis above.

**Secondary Objective 3:** For Secondary Objective 3, analyses will include individuals with chronic diseases (e.g., chronic kidney disease, lung disease including COPD and asthma, diabetes, identified by ICD-10 codes). For each disease, we will calculate COVID-19 diagnosis incidence, unadjusted and adjusted HRs and VEs, as described for the primary analysis above.

**Secondary Objective 4:** For Secondary Objective 4, analyses will include individuals who are immunocompromised (e.g., HIV, cancer, transplant, immunosuppressive medications identified by ICD-10 codes, registries, and pharmacy data). We will calculate COVID-19 diagnosis incidence, unadjusted and adjusted HRs and VEs, as described for the primary analysis above.

**Secondary Objective 5:** For Secondary Objective 5, analyses will include individuals with autoimmune conditions (e.g., rheumatoid arthritis, inflammatory bowel disease, psoriasis, psoriatic arthritis, multiple sclerosis, systemic lupus erythematosus). We will calculate COVID-19 diagnosis incidence, unadjusted and adjusted HRs and VEs, as described for the primary analysis above.

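### Table 3 codes BMI in one set of absolute bands for everyone aged 12 and over, so BMI screening and adjustment may be incomplete in the 12-17 stratum; the effect is small

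*Protocol*

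**What the plan says.** - Protocol, section 7.3, Table 3: the BMI row takes the most recent measurement in the two years (730 days) before the index date and codes it as "<18.5, 18.5 - <25, 25 - <30, ≥30 - <35, 35 - <40, 40 - <45, ≥45, Unknown". No other coding is given for any age group.
- Protocol, Version History, version 1.1: "Addition of adolescents (12-17 years". Section 6.1 now admits anyone "Aged $\geq 12$ years at index date".
- Table 3 codes age as "12-17, 18-44, 45-64, 65-74, 75" and over, so 12-17 is one level. Section 6.2 uses the same grouping for matching.
- For Secondary Objective 1, section 8.4 states the plan as follows: "analyses will be stratified by sex and age category (12-17 years, 18-44 years, 45-64 years, 65-74 years, and 75+ years) at index date". An adjusted VE is to be given in each stratum.
- Section 7.3 on how covariates are used: the Table 3 variables are "considered in analyses when feasible and appropriate as covariates or stratification variables". A variable counts as a potential confounder when its absolute standardized difference (ASD) exceeds 0.1. On recoding: "Some categories of a categorical variable with small sample sizes may be redefined or combined into one category".

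**The concern.** A fixed BMI value does not mean the same relative weight at 12 as at 17. Inside a single 12-17 age category nothing else in the model separates age from weight, so one band can hold a younger adolescent of high relative weight and an older one of ordinary relative weight.

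Two steps depend on this coding. The ASD screen sees an obesity imbalance only through the bands, so it can register a smaller difference than exists. The adjusted model then removes only the part of the confounding that the bands capture. At stake is the adjusted VE in the 12-17 stratum.

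**Working it through.** The protocol states no figure on this point, so there is nothing to reproduce. The check asks how much the bands could lose.

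**From the protocol (Table 1).** Members aged 12 to <18: 341,464. Members aged 12 and over: 341,464 + 2,942,731 + 432,045 + 270,091 = 3,986,331. Share: 341,464 / 3,986,331 = 8.6%.

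**Assumed, not in the protocol.** BMI is log-normal at each year of age, with medians 18.0, 18.6, 19.3, 20.0, 20.6 and 21.2 at ages 12 to 17, or all 8% higher. Log-SD is 0.16 to 0.28. The obesity cut-point rises linearly from 24 at age 12 to 29.5 at 17. Ages are equally represented and cohorts are of equal size. Obesity carries a risk ratio of 1.3.

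**Step 1: confounding with no BMI adjustment.** For obesity prevalence p1 (vaccinated) and p0 (unvaccinated), the HR is multiplied by (1 + 0.3·p1)/(1 + 0.3·p0). With 20% versus 12%: 1.060/1.036 = 1.023. At a true VE of 50% this is 50 × 0.0232 = 1.2 VE points; at 90% it is 10 × 0.0232 = 0.2.

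**Step 2: what remains after stratifying on the Table 3 bands.** The Mantel-Haenszel ratio across bands is compared with the crude ratio on the log scale. The last column takes obesity at 16% versus 12%, for which the ASD of obesity itself is 0.04 / √[(0.1344 + 0.1056)/2] = 0.115. The band ASD uses the multi-category (Mahalanobis) form, since the protocol names no formula.

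| Medians | Log-SD | Below 18.5 | Obese | Obese with BMI <30 | Confounding left | VE shift at 50% | Band ASD, 16% v 12% |
|---|---|---|---|---|---|---|---|
| base | 0.16 | 37% | 2.7% | 78% | 35% | 0.40 | 0.092 |
| base | 0.20 | 39% | 6.1% | 67% | 35% | 0.40 | 0.092 |
| base | 0.25 | 41% | 10.8% | 56% | 32% | 0.37 | 0.094 |
| base | 0.28 | 42% | 13.5% | 50% | 31% | 0.35 | 0.095 |
| +8% | 0.16 | 22% | 7.4% | 74% | 45% | 0.52 | 0.084 |
| +8% | 0.20 | 26% | 12.3% | 62% | 41% | 0.47 | 0.088 |
| +8% | 0.25 | 30% | 17.7% | 51% | 35% | 0.41 | 0.092 |
| +8% | 0.28 | 32% | 20.4% | 46% | 33% | 0.37 | 0.094 |

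Four rows (base with 0.28; +8% with 0.20, 0.25 and 0.28) give an obesity prevalence in or next to the 12-20% used in Step 1. They leave 31-41% of the confounding, or 0.35-0.47 VE points at 50%. At a true VE of 90% the shift is 0.1 point or less in every row.

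**Step 3: the screen.** In every row an obesity imbalance with ASD 0.115 shows as 0.084-0.095 in the bands, below the 0.1 threshold. If BMI is then left out, the HR factor is 1.048/1.036 = 1.0116, or 0.6 VE points at 50% and 0.1 at 90%. This applies if the screen is run within the stratum. Section 7.3 says that selection is repeated by dose cohort, and does not mention age stratum.

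**Step 4: pooled models.** A shift of 0.5 points in 8.6% of the population is about 0.5 × 0.086 = 0.04 points overall.

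**The case against.** The strongest reply is that this is a coding preference with an immaterial effect. Table 3 lists possible covariates only, BMI enters only if imbalanced, and absolute bands still order adolescents by BMI and apply equally to both cohorts. Age group stays in every adjusted model, and a separate statistical analysis plan is scheduled in Table 6. Adolescents are included only once the vaccine is authorized and recommended for them (section 4.1), while accrual ends on 12/31/2021.

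Much of this stands. The effect is small, the stratum is conditional, and the age-group term absorbs the average difference between adolescents and adults in pooled models.

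It does not remove the point. The clause on feasible and appropriate use governs whether BMI is used, not how it is coded. Recoding is allowed for small categories, which is a rule about size and not age. Table 3 marks the income and frailty rows as still to be set, but gives BMI hard cut-points. This is a stated coding, not detail left to a later plan.

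**Conclusion.** The point holds as a minor one. One set of absolute BMI bands serves all ages from 12, so in the 12-17 stratum of Secondary Objective 1 the screen can understate an obesity imbalance and the adjustment may be incomplete. The size is about half a VE point or less after adjustment at a true VE of 50%, about 0.6 if the screen drops BMI, and about 0.1 at 90%. All of this rests on the assumed BMI distributions, cut-points, imbalance and risk ratio above. The effect on the primary objectives is negligible.

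A reader might go further in three ways that the protocol does not support:

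- That most obese adolescents land in lower bands. The protocol gives no adolescent obesity cut-points or BMI distribution, and the share runs from 46% to 78% across the assumptions tried.
- That BMI is poorly controlled in adolescents. The bands removed more than half of the confounding in every run, so incompletely controlled is the fair description.
- That the BMI row was overlooked when adolescents were added. No earlier version is available, and the version history says nothing about covariates.

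**What to change.** In Table 3, keep the listed bands for ages 18 and over. For ages 12-17, use BMI-for-age-and-sex categories: underweight, normal, overweight, obese and unknown. Compute them at the age on the date of measurement, not at the index date, because the measurement may be up to 730 days old. In pooled models, enter BMI as an age-specific covariate, either with separate adolescent levels or with the categories nested within the 12-17 and 18-and-over groups.

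The cost is one extra derivation from height, weight, age and sex in the health record, plus a few more model levels. No new data collection is needed.

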### 6.2 Index Dates

All individuals meeting criteria in Section 6.1 will be included in analyses. Index dates will be assigned at each analysis. For vaccinated individuals, the index date for Primary Objectives 1-2 and Secondary Objectives 1-13 will be the date of receipt of the second dose of Moderna COVID-19 vaccine. For Secondary Objectives 14-15 among individuals who receive only 1 dose of Moderna COVID-19 vaccine, the index date for vaccinated individuals will be the date of receipt of the first dose of Moderna COVID-19 vaccine.

The index date for the comparison group will depend on the analysis. The comparison group will comprise a similar population meeting criteria in Section 6.1 who are unvaccinated at the index date. For the first and second interim analyses (if sample size allows), unvaccinated individuals will be randomly selected and n:1 matched to the vaccinated individuals by age (12-17 years, 18-44 years, 45-64 years, 65-74 years, and  $\geq 75$  years), sex, and race/ethnicity (Non-Hispanic White, Non-Hispanic Black, Hispanic, Non-Hispanic Asian, and Other/Unknown). The matching ratio will depend on the sample size of the unvaccinated population, between 1:1 to 5:1. The index date for the unvaccinated match will be the same as his/her matched vaccinated counterpart.

For the subsequent interim analyses and final analysis, we expect that there will be insufficient unvaccinated individuals for 1:1 matching, as COVID-19 vaccination is expanded to the general

population. If this is the case, unvaccinated individuals will be randomly selected and matched to the vaccinated individuals by the distribution (frequency) of age, sex, and race/ethnicity of vaccinated individuals. Since frequency matching is not conducted on the individual level, an index date will be assigned to unvaccinated individuals based on the distribution of calendar time of vaccinated individuals on the vaccination (index) date in each age, sex, and race/ethnicity stratum. For example, if 5% of vaccinated individuals are vaccinated during the week of February 1, 2021, 5% of unvaccinated individuals will be assigned an index date of February 1, 2021. Hence, the distribution of index dates between the vaccinated group and the unvaccinated group will be matched. For each interim analysis during the accrual period (December 2020 to December 2021), the comparison group will be assessed and assigned with index dates independently based on all available data.

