## 7 Measures

### 7.1 Exposure Definition

The primary exposure for this study (Primary Objectives 1-2, Secondary Objectives 1-13) will be receipt of 2 doses of Moderna COVID-19 vaccine received  $\geq 24$  days apart (allowing a 4-day grace period prior to the recommended interval of 28 days) during the accrual period. The exposure for Secondary Objectives 14-15 will be 1 dose of Moderna COVID-19 vaccine among individuals who received only 1 dose during the accrual period, and the exposure for Secondary Objective 9 will be receipt of 2 doses of Moderna COVID-19 vaccine during the accrual period, with either dose given concomitantly with another vaccine.

- CVX code: 207
- KPSC Immunization ID and description:
  - 124285 COVID-19, mRNA, LNP-S, PF (Moderna)
  - 124287 COVID-19 vaccine, Moderna, external administration
- Manufacturer: Moderna, Inc
- Product name: Moderna COVID-19 Vaccine
- NDC 10/NDC 11 Labeler Product ID (vial): 80777-273-10 or 80777-0273-10

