| Systemic lupus erythematosus                                                                     | Yes, No                                                                                   |
| Health care utilization                                                                   |                                                                                           |
| Number of virtual and outpatient encounters                                                      | 0, 1-4, 5-10, 11+                                                                         |
| Number of emergency encounters                                                                   | 0, 1, 2+                                                                                  |
| Number of inpatient encounters                                                                   | 0, 1, 2+                                                                                  |
| Preventive care - with other vaccinations, screenings, and well-visits from all settings         | Yes, No                                                                                   |

|                                                                                                                    | Categories                          |
|--------------------------------------------------------------------------------------------------------------------|-------------------------------------|
| Chronic diseases                                                                                            |                                     |
| Kidney disease                                                                                                     | Yes, No                             |
| Heart disease                                                                                                      | Yes, No                             |
| Lung disease                                                                                                       | Yes, No                             |
| Liver disease                                                                                                      | Yes, No                             |
| Diabetes                                                                                                           | Yes, No                             |

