| Other variables                                                                                             |                                     |
| KPSC physician/employee status at index date                                                                       | Yes, No                             |
| Frailty index in year prior to index date (-365 to -1 day, inclusive), using method by Kim et al. [15]             | To be determined based on quartiles |
| History of COVID-19 diagnosis (from March 1, 2020 to index date, inclusive)                                        | Yes, No                             |
| History of SARS-CoV-2 molecular test performed (from March 1, 2020 to index date, inclusive), regardless of result | Yes, No                             |
| Concomitant vaccine                                                                                                | Yes, No                             |
| Immunocompromised status                                                                                    | Yes, No                             |
| HIV/AIDS any time prior to index date                                                                              | Yes, No                             |
| Leukemia, lymphoma, congenital immunodeficiencies, asplenia/hyposplenism any time prior to index date              | Yes, No                             |
| Organ transplant any time prior to index date                                                                      | Yes, No                             |
| Immunosuppressant medications at index date                                                                        | Yes, No                             |

\* Charlson comorbidities include myocardial infarction, congestive heart failure, peripheral vascular disease, cerebrovascular disease, connective tissue disease, dementia, chronic pulmonary disease, connective tissue disease, peptic ulcer disease, diabetes mellitus, paraplegia and hemiplegia, renal disease, liver disease, cancer, metastatic solid tumor, human immunodeficiency virus (HIV), and acquired immunodeficiency syndrome (AIDS)

The covariates included in adjusted analyses will be determined by scientific relevance, association with exposure, and data availability. Specifically, we will select covariates by following these steps:

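### In the 2-dose cohort analyses the health care utilization look-back runs past dose 1, so adjusting for encounter counts can bias VE if the dose-1 visit is counted

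*Protocol*

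**What the plan says.** Section 6.2 states that for recipients in Primary Objectives 1-2 and Secondary Objectives 1-13 the index date "will be the date of receipt of the second dose of Moderna COVID-19 vaccine". Section 7.1 requires at least 24 days between doses, "allowing a 4-day grace period prior to the recommended interval of 28 days". Under individual matching, "The index date for the unvaccinated match will be the same as his/her matched vaccinated counterpart". Under frequency matching, comparators receive index dates drawn from the recipients' calendar distribution. Either way, a comparator must be unvaccinated at the index date.

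In section 7.3, Table 3 places the utilization variables under "Variables to be assessed in the year prior to index date (-365 to -1 day, inclusive". The first of these is "Number of virtual and outpatient encounters", banded 0, 1-4, 5-10 and 11+. Another is "Preventive care - with other vaccinations, screenings, and well-visits from all settings". COVID-19 history is a separate row with its own window: "History of COVID-19 diagnosis (from March 1, 2020 to index date, inclusive".

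Table 3 variables are to be "considered in analyses when feasible and appropriate as covariates or stratification variables". The selection steps below the table review distributions, flag a variable as a potential confounder when its ASD exceeds 0.1, and carry all flagged variables into the adjusted analyses.

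**The concern.** A baseline covariate should not be able to record the exposure. For 2-dose recipients, the last four weeks or so of the one-year window lie after dose 1. The dose-1 visit, and any message or visit it prompts, can add to the recipient's count but never to the comparator's. The preventive-care row refers to other vaccinations and so appears to leave dose 1 out; the encounter rows have no such wording.

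The ASD rule cannot tell a difference that existed before vaccination from one that vaccination created. If dose-1 visits are counted, the rule reads the artefact as confounding. The adjusted model then sets recipients with no real encounter, now coded 1-4, against comparators who had real encounters. This error does not shrink with sample size, and section 9 expects 500,000 to 1,000,000 recipients. It acts as a multiplier on the HR, so it costs more VE points where VE is lower, which matters for the durability analyses by follow-up year (Secondary Objectives 12-13).

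**Working it through.** **The plan's own figures.** The protocol gives no figure on this point. Its power tables do reproduce. For 0.3 per 1,000, 80,000 per group, VE 80% and two-sided alpha 0.007, the pooled two-proportion formula gives Φ[(0.00024×√80,000 − 2.697×√(2×0.00018×0.99982)) / √(0.0003×0.9997 + 0.00006×0.99994)] = Φ(0.88) = 0.81, as Table 5 states. Moving a covariate window does not change these figures.

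**Step 1: timeline.** With dose 2 at day 0, dose 1 is at day −24 or earlier (day −28 at the recommended interval). Both lie inside −365 to −1.

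**Step 2: would the artefact pass the screen?** Let z be the share of each group with truly no encounter (assumed 10-20%), and suppose every recipient gains one. Recipients then have a zero share of 0, and ASD = z/√(z(1−z)/2).
- z = 0.1: 0.1/√0.045 = 0.47
- z = 0.2: 0.2/√0.08 = 0.71

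If only half of these recipients gain a counted encounter, the ASD is 0.05/√((0.09+0.0475)/2) = 0.19 at z = 0.1 and 0.10/√((0.16+0.09)/2) = 0.28 at z = 0.2. Assumed negative binomial counts (mean 3, 5 or 8; dispersion 1 or 2) over all four bands give 0.32 to 0.82. All of these exceed 0.1.

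**Step 3: effect on VE, two-band version.** Let r be the diagnosis rate of people with no encounter relative to those with at least one (assumed 0.3-0.7). Recipients coded as having encounters then have average relative rate z·r + (1−z), which multiplies the HR.

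| z | r | HR factor | true VE 90% reads | true VE 70% reads | no effect reads |
|---|---|---|---|---|---|
| 0.1 | 0.7 | 0.97 | 90.3 | 70.9 | 3 |
| 0.1 | 0.3 | 0.93 | 90.7 | 72.1 | 7 |
| 0.2 | 0.7 | 0.94 | 90.6 | 71.8 | 6 |
| 0.2 | 0.3 | 0.86 | 91.4 | 74.2 | 14 |

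The factor is 0.86-0.97. This version considers only r below 1 and only the boundary between 0 and 1 encounters.

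**Step 4: four bands, either direction.** One encounter is added to each recipient's count, risk changes by a fixed ratio per band (assumed 1.1 to 1.5, or the inverse), and a Poisson rate model adjusted for band is solved for the HR. For counts with mean 3 and dispersion 1, and a ratio of 1.5:
- Band 1-4 in recipients holds 0.250 with true count 0 (rate 1) and 0.434 with true count 1-3 (rate 1.5). The average is (0.250 + 0.434×1.5)/0.684 = 1.317, against 1.5 in comparators: 0.878.
- The same calculation gives 0.899 for band 5-10 and 0.917 for 11+.
- The model pools these to 0.889. A true VE of 90% reads 1 − 0.1×0.889 = 91.1%, and 70% reads 1 − 0.3×0.889 = 73.3%.
- With the inverse ratio the factors are 1.183, 1.152 and 1.125, pooled 1.175. Then 90% reads 88.3% and 70% reads 64.8%.

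These are the extremes over all the assumed distributions. With ratios up to 1.25 per band, 90% reads 89.1-90.7 and 70% reads 67.4-72.0.

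**Step 5: is COVID-19 history affected in the same way?** Section 9 assumes 30 diagnoses per 1,000 unvaccinated in 4 months, which is 30×28/121.75 = 6.9 per 1,000 in 28 days (5.9 in 24 days, 10.3 in 42). Prevalence of history at the end of 2020 is 295,395/3,986,331 = 7.4% (Table 2 over the Table 1 ages 12 and above). Suppose dose 1 prevented every infection over 42 days. Comparator prevalence would be 0.0741 + 0.0103×0.926 = 0.0836, an ASD of about 0.036. With an assumed HR of 0.1 for prior infection, the HR ratio is (1−0.9×0.0741)/(1−0.9×0.0836) = 1.009. That is about 0.1 VE point at 90% and 0.3 at 70%.

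**The case against.** The protocol never says that a vaccination visit counts as an encounter. Section 4 lists immunization as a separate data source. Some doses are given externally (sections 7.1 and 13) and may leave no encounter. Table 3 lists possible covariates only, and the first selection step lets the analyst merge categories, so an empty zero band could be noticed. Section 6.1 removes people with neither utilization nor vaccination in two years, which lowers the zero share among comparators, so an equal z in both groups is a simplification. The rule for counting encounters could sit in an analysis plan that is not shown. All of this stands, and it makes the bias conditional. It does not remove the point: the window is fixed to the day and tied to dose 2, contacts prompted by dose 1 fall inside it even if the visit itself is not counted, and the screen still triggers when only half of inactive recipients gain an encounter.

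A reader might infer three stronger things that the documents do not support.
- **VE is biased, and upward.** The sign depends on whether low users have lower or higher diagnosis rates, which the protocol does not report.
- **COVID-19 history is contaminated in the same way.** Follow-up starts from dose 2 and outcomes count from day 14, so infection before the index date is a genuine confounder in both groups. Its row runs through the index date, and its dose-1 component is negligible (Step 5).
- **Both doses enter the covariate window in the test-negative design.** Section 10.1 states no look-back and does not cite Table 3, and its screen compares cases with controls, so the ASDs above do not carry over.

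**Conclusion.** The point holds for the utilization variables in the 2-dose cohort analyses (Primary Objectives 1-2, Secondary Objectives 1-13). As written, the look-back includes time after exposure began, and the ASD rule would treat a difference made by the exposure as confounding. If dose-1 visits are counted, the possible error is under 1 to about 2 VE points at a true VE of 90% and up to about 5 points at 70%, in either direction. These sizes rest on assumed encounter distributions, risk ratios and one added encounter per recipient; none of these comes from the protocol. Planned power is unaffected. Secondary Objectives 14-15 are indexed at dose 1 and are not touched. The case does not extend to re-anchoring every Table 3 variable: measuring covariates at time zero over a shared calendar window is otherwise defensible.

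**What to change.** In section 7.3, for the 2-dose analyses:
- End the utilization look-backs (encounter counts and preventive care) the day before dose 1 for recipients.
- End them the same number of days before the index date for comparators: the matched recipient's dose interval, or the stratum median under frequency matching.
- State that COVID-19 vaccination visits are not counted as encounters.
- Keep COVID-19 history assessed through the index date.

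If the Table 3 utilization variables are used in the test-negative design, exclude COVID-19 vaccination visits there too. The dose-2 anchor can be kept as a sensitivity analysis.

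The cost is a short addition to section 7.3, minor programming, and utilization covariates that are about four weeks older.
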